**Figure 1 figure1:**
[figure not shown]
Flowchart of the study phases.

**Figure 2 figure2:**
[figure not shown]
Flowchart of the randomized controlled trial. BDI-II: Beck Depression Inventory-II; MINI: Mini-International Neuropsychiatric Interview.

### Inclusion and Exclusion Criteria

Turkish participants living in Turkey are eligible if they are aged between 18 and 55 years, have internet access, have both a personal computer (PC) and a smartphone or tablet, and have mild to moderate depressive symptoms (Beck Depression Inventory-II [BDI-II] score between 10 and 29) [35]. Participants will be excluded if they have a BDI-II score above 29 or a medium-to-high suicidal risk (according to the Mini-International Neuropsychiatric Interview [MINI]), and they are advised to contact a psychiatrist or clinical psychologist by sending them an email [36,37].

### Recruitment

Recruitment will take place in the general population in Turkey until the end of the project or earlier if the sample size will be achieved. A total of 2 psychologists will be involved in the recruitment, assessments, and therapy delivery: the clinical psychologist will deliver the therapy messages, follow up with the administration of the assessments, message management for admission to the study, and convince dropouts to continue, whereas the other psychologist (Bachelor’s degree) will actively recruit participants for the study. Announcements will be placed online at health-related social media sites and offline at several meeting points at the university. These announcements will contain a link to the research website with detailed information about the study. Respondents who are interested can apply by sending an email to the clinical psychologist. A link to the screening and an informed consent form will be emailed to the respondent. The screening includes the BDI-II and MINI questionnaires; access to a PC and smartphone or tablet; and demographic information of the respondents, such as name, surname, email address, age, and gender. Applicant admission is done by checking the BDI-II and MINI scores of applicants manually.

### Measures

Assessments will take place before randomization (baseline), directly after completing the treatment (2 months after baseline), and finally, 4 months after baseline as a follow-up assessment. All outcomes are self-assessed through online questionnaires and can take up to 20 to 30 min to complete. Participants will receive 15 TL (Turkish Lira, the local currency) in total only if completing all 3 assessments. An overview of the measures used per assessment is given in Table 1.

#### Sociodemographic and Additional Information

At baseline, sociodemographic information about the participant will be collected by asking questions about the following: sex, age, educational level, employment, long-term relationship or partner status, living situation, chronic physical illness, chronic psychological illness, and psychological or psychiatric treatment status.

#### Primary Outcome: Depressive Symptoms

To measure depressive symptoms as the primary outcome, the Turkish version of the self-report BDI-II will be used at baseline, posttreatment, and follow-up [38]. It has 21 items in total describing depressive symptoms. Each item is scored on a 4-point scale, with a range of 0 (not at all) to 3 (severe). The total score ranges from 0 to 63. The BDI-II has good psychometric properties for online administration [39]. The Turkish version has been proven to have good reliability and validity [38,40]. The cut-off scores are 0 to 9 for minimal, 10 to 29 for moderate, and 30 to 63 for severe depression.

#### Secondary Outcomes

##### Anxiety Symptoms

Anxiety will be measured with the State-Trait Anxiety Inventory (STAI), a measure of trait and state anxiety by self-report [41]. The STAI has 40 items in total, of which 20 items are allocated in the state scale (S-Anxiety) and 20 items in the trait scale (T-Anxiety). The S-Anxiety scale is intended to assess the intensity of current feelings of anxiety, whereas the T-Anxiety scale assesses feelings of anxiety in general. All items are rated on a 4-point scale (from almost never to almost always). A higher score indicates greater anxiety levels. The STAI is available in Turkish and has been shown to be a valid and reliable measure [42].

**Table 1 table1:** Overview of instruments per assessment.

Instruments	Number of items	Baseline	Posttreatment	Follow-up
Sociodemographic and additional information	20	✓^a^	—^b^	—
Depressive symptoms (Beck Depression Inventory-II)	21	✓	✓	✓
Anxiety (State-Trait Anxiety Inventory)	40	✓	✓	✓
Worry (Penn State Worry Questionnaire)	16	✓	✓	✓
Stress (Perceived Stress Scale)	10	✓	✓	✓
General Self-Efficacy	10	✓	✓	✓
Quality of life (EuroQol-5D-5L)	6	✓	✓	✓
Satisfaction and log data	8	—	✓	—
Usability and acceptability	40	—	✓	—

^a^These instruments will be assessed during the trial.

^b^These instruments will only be assessed once during the trial.

##### Worry

The Penn State Worry Questionnaire (PSWQ) will be used to measure pathological worry [43]. The PSWQ has 16 items in total. Each item can be scored on a 5-point scale from 1 (not at all typical of me) to 5 (very typical of me), with a total score varying from 16 to 80. The PSWQ has good psychometric properties to use in an online format [44]. The PSWQ has been translated into Turkish and shown to be valid and reliable in a Turkish sample [45].

##### Stress

The Perceived Stress Scale (PSS) will be used to measure the perception of stress [46]. It consists of 14 items originally, but it can also be assessed in a short form of 10, for which the total score range is 0 to 40 [47]. Each item is rated on a 5-point scale, ranging from 0 (never) to 4 (very often). The Turkish version of the PSS has been shown to be valid and reliable [48]. For this study, the short form consisting of 10 items will be used.

##### Self-Efficacy

The General Self-Efficacy (GSE) scale is a measure to assess self-efficacy beliefs [49]. The GSE scale contains 10 items, which are rated on a 4-point scale from 1 (not at all true) to 5 (exactly true). The total score varies from 10 to 50. The Turkish version will be used, which has been shown to have good reliability and validity [50].

##### Quality of Life

To measure quality of life, the EuroQol-5D-5L (EQ-5D-5L) will be used [51]. It consists of 5 items each measuring different dimensions of health status (mobility, self-care, usual activities, pain or discomfort, and anxiety/depression). The items are rated on a 5-point scale from level 1 to level 5 (no problems, slight problem, moderate problem, severe problem, and extreme problem). All the answers to each item are combined, resulting in 3125 possible health states, ranging from 11,111 (full health) to 55,555 (worst health). Furthermore, there is an EQ-visual analog scale measuring a global rating of self-perceived health. This is scored by 0 (the worst health you can imagine) to 100 (the best health you can imagine). The EQ-5D-5L is valid and reliable for use in an online format [52]. The Turkish version has good validity and reliability properties [53].

##### Satisfaction and Log Data

After completion of the intervention, participants will be asked to define their satisfaction with each module in the intervention (ie, “Was this lesson useful to you?”). The answers can be rated on a 5-point Likert scale from 1 (not at all) to 5 (very useful). Finally, log data will be collected by using the following parameters: type of device, last activity, first session, app version, and usage duration, which will be monitored until the follow-up assessment.

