**Methods:**

Participants will be recruited through announcements in social media and the Middle East Technical University. Adults (18-55 years) with mild to moderate depressive symptoms (Beck Depression Inventory-II [BDI-II] score between 10-29) will be included in the study. Participants with a medium-to-high suicidal risk (according to the Mini-International Neuropsychiatric Interview) will be excluded. A 3-armed randomized controlled trial with a waiting control group will be utilized. A sample size of 444 participants will be randomized across 3 groups. The first experimental group will receive direct access to the Web version of the intervention; the second experimental group will receive direct access to the mobile app of the intervention as well as automated supportive short message service text messages based on PST. The control group consists of a wait-list and will gain access to the intervention 4 months after the baseline. The intervention is based on an existing PST for the Turkish population, *Her Şey Kontrol Altında* (HŞKA), consisting of 5 modules each with a duration of 1 week and is guided by a clinical psychologist. The primary outcome is change in depressive symptoms measured by the BDI-II. Secondary outcomes include symptoms of anxiety, stress, worry, self-efficacy, and quality of life. Furthermore, satisfaction with, usability and acceptability of the intervention are important features that will be evaluated. All outcomes will take place online through self-assessment at posttest (6-8 weeks after baseline) and at follow-up (4 months after baseline).

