HŞKA consists of 5 modules over 5 weeks, consisting of text, photos, videos, and exercises. Briefly, the length of each module is 1 page and the duration of videos 2 to 3 min. First, participants indicate what they think is important in their lives; they make a list of their problems and worries, and they categorize their problems into 3 groups: (1) unimportant problems, which are not related to what they think is important in their lives; (2) important but solvable problems, which are tackled with a systematic, problem-solving approach consisting of 6 steps (which consists of defining the problem, developing alternative solutions, choosing the best solution, making a plan for the solution, implementing the solution, and evaluation); and (3) important but unsolvable problems, such as having lost someone through death or having a chronic physical illness and making a plan for how to live with it. Each session includes about 1.5 A4 pages long text with explanations and examples and short videos about the theory; at the end of each session, exercises can be made. The core of the intervention is the 6-step problem-solving procedure, which teaches users this technique for several of their important but solvable problems. The idea is that by mastering this technique, people will regain mastery of their problems and ultimately their lives. Participants receive feedback on their homework assignments in brief weekly online messages from a clinical psychologist with a PhD degree in Clinical Psychology (first author). Those who have not sent their assignments will receive a reminder within the app once a week. After 3 reminders, participants who still have not sent anything will be considered as dropouts.

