### Sample Size

In this RCT, 2 experimental groups (receiving the intervention by either the internet or a mobile app) will be compared with a waiting list control group. The sample size is calculated based on an expected difference of Cohen *d*=0.45 (moderate) between 1 of the experimental groups and the control group as in previous studies [22,25]. “ *F* tests-analysis of variance repeated measures” will be applied in G-Power Statistical Power Analysis program version 3.1 and used for sample size calculation [55]. To obtain a power of .80 for a 1-tailed test and an alpha of .05, a total of 234 participants for 3 groups is needed. However, high attrition rates at posttest (25.0%) and at follow-up (30.0%) are expected based on previous studies [24,25]. Therefore, the sample size will be increased to 444 participants in total (allowing an attrition of 25.0%*30.0%=52.5%). This means that 148 participants are required at baseline for each group.

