### Statistical Analyses

The study will be reported in accordance with the consolidated standards of reporting trials guidelines [57]. The data obtained from the study will be evaluated and data tables created using the Statistical Package for Social Sciences version 25.0 statistical software program [58]. The significance level will be accepted as 95% CI (*P*<.05) in all statistical analyses. Quantitative (categorical) variables will be expressed as mean, SD, and upper and lower values in this study, whereas qualitative (continuous) variables will be expressed as numbers (n) and percentage (%). The Kolmogorov-Smirnov Test will be used to examine whether the quantitative data were distributed normally. To measure the efficacy of the treatment in this study, general linear model repeated measures analysis will be used to investigate the change on the primary outcome (BDI-II) scores in dependent variables for the total sample based on the intention-to-treat principle and for analyzing missing data [59]. McNemar tests will be used to measure categorical change as a version of the Chi-square test of independence in repeated measures of dependent groups. Furthermore, the Fisher exact Chi-square tests will be used if the number of crosstabs data is insufficient and the hypothesis is not achieved. Attrition will be defined as not completing any or 1 of the posttreatment measures. The notification effect will be analyzed by comparing the dropout rates of the Web and mobile versions. Finally, the correlation coefficient and statistical significance between the quantitative variables will be calculated by 2-way Pearson correlation analysis.

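### Module satisfaction is rated only once, at posttreatment, so participants lost before then give no rating even for modules they used, and the reported mean may be too favourable

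*Protocol article*

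**What the plan says.** Under Satisfaction and Log Data, the article says that "After completion of the intervention, participants will be asked to define their satisfaction with each module in the intervention", on a scale from 1 to 5. Table 1 lists "Satisfaction and log data" as 8 items, ticked at posttreatment and at neither of the other assessments. No rating during the modules is described.

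The Measures section times the posttreatment assessment as "directly after completing the treatment (2 months after baseline), and finally, 4 months after baseline as a follow-up assessment"; the Abstract gives 6 to 8 weeks after baseline. The visit is thus tied both to finishing treatment and to the calendar.

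Two kinds of loss are defined. In Statistical Analyses, "Attrition will be defined as not completing any or 1 of the posttreatment measures". In Intervention Description, a separate rule concerns homework: "After 3 reminders, participants who still have not sent anything will be considered as dropouts". Sample Size gives an expected rate for the first kind only: "high attrition rates at posttest (25.0%) and at follow-up (30.0%) are expected based on previous studies". Per-Protocol Analysis likewise lists completing the measurements and completing the five modules as two conditions.

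The Abstract gives these measures weight: "satisfaction with, usability and acceptability of the intervention are important features that will be evaluated".

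**The concern.** A rating taken once, at the end, comes from those who are still there. Someone who works through two modules and then leaves has an opinion on both, but the plan has no occasion to record it. If people who leave tend to be less satisfied, the average over those who remain is too favourable, and a module that drives people away escapes their low marks.

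This matters because satisfaction is one of the features on which the intervention's applicability in Turkey will be judged. It also matters for comparing the two active arms. The Limitations section says the daily notifications may counteract attrition in the mobile arm. If they do, the Web ratings would come from a more selected group than the mobile ratings. How ratings are collected cannot be repaired later: no analysis plan can recover answers that were never requested.

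**Working it through.** **Inputs from the article.** 148 participants per arm; two active arms, so 296; expected attrition 25% at posttest and 30% at follow-up; 234 evaluable and 444 randomised in total; attrition in online trials that can exceed 50% (Limitations).

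**Inputs assumed.** The gap g between the mean rating of those scored and the mean that those missing would have given, and an SD of 1 for a single rating. The article gives neither.

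**Step 1: how the plan itself uses the 25%.** Retention is 0.75 × 0.70 = 0.525, and 234 / 0.525 = 445.7, so 446 against the stated 444. The figure reproduces to within 2 participants. (The 52.5% that the article labels attrition is therefore retention; attrition is 47.5%.) Per arm, 148 × 0.75 = 111 at posttest. The plan applies the 25% equally to all three arms, wait-list included.

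**Step 2: ratings missing at posttest.** Carrying that rate over to the active arms:
- per arm: 0.25 × 148 = 37 without a score, 111 with one;
- both active arms: 0.25 × 296 = 74 without, 222 with.

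**Step 3: two readings of the timing.**
- *Dated posttest sent to everyone.* Only those lost at posttest are missing: 37 per arm.
- *Completion as a condition on the person.* Those who stopped the modules but answer the posttest are missing too. The article gives no expected rate for stopping the modules, so this adds an unknown number to the 37.

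Under both readings, people lost before posttest give no rating for modules they used.

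**Step 4: effect on the mean.** With missing share m and mean R among those scored, the mean over everyone is (1 − m)R + m(R − g) = R − mg. The reported mean is too high by m × g.

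| Missing share | g = 0 | g = 0.5 | g = 1.0 | SE of the mean (SD 1) |
|---|---|---|---|---|
| 25% (n = 111 scored) | 0 | 0.125 | 0.25 | 1/√111 = 0.095 |
| 50% (n = 74 scored) | 0 | 0.25 | 0.50 | 1/√74 = 0.116 |

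In standard errors, the excess for g of 0.5 to 1.0 is 1.3 to 2.6 at 25% missing and 2.2 to 4.3 at 50%. The standard error serves only as a yardstick, since the article states no test or threshold for satisfaction.

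**Step 5: comparison of Web and mobile.** With the same gap in both arms, the spurious difference is (m_Web − m_mobile) × g. As an illustration, 50% missing in Web and 25% in mobile gives 0.25 × g, or 0.125 to 0.25 points in favour of Web for g of 0.5 to 1.0. With equal retention and equal gaps it is zero.

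**The case against.** A reader might infer that everyone who stops the modules early is never scored, that this is at least a quarter of participants on the plan's own figures, and that satisfaction is therefore overstated. The documents do not support any of the three as fact.

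- *Never scored.* The posttest has a calendar date, Table 1 puts satisfaction in the same column as the BDI-II, and the per-protocol definition separates finishing modules from finishing measurements. Non-completers may well receive the form; nothing excludes them.
- *At least a quarter stop early.* The 25% is missing posttest measures across the whole sample. Stopping treatment is defined separately, with no expected rate, and applying the 25% to the active arms is itself an extrapolation.
- *Is overstated.* The direction is plausible, but its size rests on a gap the article does not give and that could be zero.

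Other points also have force. Usage logs run until follow-up and will show early disengagement. Acceptability has its own questionnaire, and pilot studies examine acceptance and usability. A journal article may leave out form details such as an answer for unused modules, so their absence is not a fault.

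These arguments narrow the point but do not remove it. Logs contain no ratings, the acceptability questionnaire is also given only at posttreatment, and the single late rating is something the article fixes rather than omits.

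**Conclusion.** The point holds in a limited form. One module rating at posttreatment loses the opinions of everyone who has left by then, including opinions on modules they used. If the 25% posttest attrition applies to the active arms, that is about 37 of 148 per arm, and more if completion is a condition for being asked. The resulting excess in the mean is 0.25 × g: nothing if those missing are equally satisfied, and 0.13 to 0.25 points for an assumed gap of 0.5 to 1.0. Web and mobile would be affected unequally only if retention or the gap differs between them; the Limitations section treats better mobile retention as a possibility, not as an expectation.

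Severity is minor. Satisfaction is a descriptive secondary measure, and the BDI-II comparison is not affected.

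**What to change.** 1. Show the one-item usefulness question in the platform at the end of each module's content. Do not make it depend on submitting the exercise: people who stop are those who send no assignments, so a prompt tied to submission would miss the same people.
2. State in Satisfaction and Log Data, and in Table 1, that the posttest satisfaction and usability forms go to every active-arm participant at the fixed posttest date whether or not the modules were finished, with an answer for a module not used.
3. Report each module's rating by arm with three numbers: responding, opening the module, and randomised.

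The cost is one extra click per module, a small platform change and a revision of two places in the text. The satisfaction figure may turn out less favourable. The remedy is incomplete: a person's last, unfinished module may still go unrated, which the denominators in item 3 would at least make visible.

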##### Usability and Acceptability

To test the final version of the Web and mobile app of the intervention, the usability and acceptability will be measured. A questionnaire developed by Çetin Kaya [54] about acceptance of the technology will be used. It consists of 3 parts: first, the general use of electronic services (e-services) and second, the acceptance of the e-service concerned, which consists of 40 items (of which 2 have been removed from this study because of irrelevance). The questionnaire has 13 subscales: perceived application mobility, perceived device mobility, expected benefit, informational influence, intention to use e-service, perceived behavioral control, perceived enjoyment, value to personalization, perceived usability, trust in the e-service, perceived ubiquity, value expressiveness, and value to incentive. This questionnaire has good psychometric properties in terms of validity and reliability [54].

### Sample Size

In this RCT, 2 experimental groups (receiving the intervention by either the internet or a mobile app) will be compared with a waiting list control group. The sample size is calculated based on an expected difference of Cohen *d*=0.45 (moderate) between 1 of the experimental groups and the control group as in previous studies [22,25]. “ *F* tests-analysis of variance repeated measures” will be applied in G-Power Statistical Power Analysis program version 3.1 and used for sample size calculation [55]. To obtain a power of .80 for a 1-tailed test and an alpha of .05, a total of 234 participants for 3 groups is needed. However, high attrition rates at posttest (25.0%) and at follow-up (30.0%) are expected based on previous studies [24,25]. Therefore, the sample size will be increased to 444 participants in total (allowing an attrition of 25.0%*30.0%=52.5%). This means that 148 participants are required at baseline for each group.

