### Randomization

Participants will be randomly assigned to 1 of the 2 experimental groups or to the control group after the first assessment (at baseline) based on 1:1:1 randomization. The allocation schedule will be generated using an online randomization tool [56], which will be performed and communicated to the patient by an independent researcher. Block randomization will be used with blocks of 9 allocations each. Furthermore, 2 strata will also be used based on age: 1 stratum for 18 to 24 years and another for 25 to 55 years. Participants will be informed about the randomization outcome by email after completing the baseline assessment. Participants in the experimental groups receive a Web link to subscribe free to the intervention with a special code. Afterwards, the participants are required to create an account on the platform with their personal code and self-chosen password. The mobile app will be free to download in the App Store and Google Play Store; however, the intervention will not be open to the general public. Blinding the participants in this RCT will not be possible; however, the statistician is blinded to group assignment.

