### Limitations

Although online guided self-help for depressive symptoms is promising, there are some points to consider. First, in a previous study among Turkish migrants with depressive symptoms, the sample size was not large enough to detect a small to moderate effect [25]. Recruitment was difficult, and the suicidal risk was moderate to high in the same study. It is expected that the same difficulties will be encountered during this trial. Second, attrition is generally high in online intervention trials and can be more than 50% [63,64]. In the study of Ünlü Ince et al [25], attrition was even higher, which led to missing data. It is expected that attrition in this study will be comparable with that of online intervention studies; however, the daily automated notifications in the mobile experimental group may counteract such high attrition rates. Finally, this study will only evaluate the severity of depressive symptoms, which means it will not be possible to say anything about recovery from a depressive disorder.

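### The 52.5% called attrition in the sample size is the share retained: 444 covers about 47.5% loss, and the rates behind it conflict with the Limitations section

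*Protocol article*

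**What the plan says.** The Sample Size section sets the evaluable target: "To obtain a power of .80 for a 1-tailed test and an alpha of .05, a total of 234 participants for 3 groups is needed". It is built on an "expected difference of Cohen *d*=0.45 (moderate) between 1 of the experimental groups and the control group". With equal allocation (Randomization section: "based on 1:1:1 randomization"), 234 is 78 per arm.

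The section then says that "high attrition rates at posttest (25.0%) and at follow-up (30.0%) are expected based on previous studies [24,25"], and draws the consequence: "the sample size will be increased to 444 participants in total (allowing an attrition of 25.0%*30.0%=52.5"%). It closes with the arm size: "This means that 148 participants are required at baseline for each group".

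In the Discussion, the Limitations section says that "attrition is generally high in online intervention trials and can be more than 50% [63,64"]. Of the earlier trial of this intervention in Turkish migrants (reference 25) it says that "attrition was even higher, which led to missing data". It expects attrition in the present trial to be similar to that of online trials generally, and adds that the daily notifications in the mobile arm may offset it.

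**The concern.** The sentence that justifies the enrolment target contains an equation that does not hold, and it calls a retained share a loss. A reader, funder or monitor would take from it that more than half of the sample can be lost while the required 234 remain. That is not so.

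The second problem makes this worse. Reference 25 is one of the two sources given for 25% and 30%, which compound to less than 50%, yet the Limitations section puts that study's attrition above a level of more than 50%. The mislabel hides the conflict: an allowance of 52.5% seems to cover a loss just over one half, and the true allowance of 47.5% does not.

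**Working it through.** **Inputs, all from the Sample Size section unless noted:** d = 0.45; alpha 0.05; power 0.80; 1-tailed test; 234 evaluable in total; losses of 25% (posttest) and 30% (follow-up); 444 randomised, 148 per arm; 1:1:1 allocation (Randomization section).

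**1. The printed equation**
- Product as printed: 0.25 × 0.30 = 0.075, or 7.5%.
- Retention after sequential losses: (1 − 0.25) × (1 − 0.30) = 0.75 × 0.70 = 0.525.
- Attrition: 1 − 0.525 = 0.475, or 47.5%.

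**2. Reproducing 444**
- Per arm: 234/3 = 78, and 78/0.525 = 148.57. Cut to 148, this gives 3 × 148 = 444.
- In total: 234/0.525 = 445.7, rounded up to 446, or 447 with 149 in each arm.
- The target therefore comes from dividing by 0.525 as retention.

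**3. What 444 leaves**

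| Loss | Remaining of 444 | Per arm | Randomised number needed for 234 |
|---|---|---|---|
| 47.5% (25%, then 30%) | 233.1 | 77.7 | 446 |
| 52.5% (as printed) | 210.9 | 70.3 | 493 |

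Break-even loss: 1 − 234/444 = 47.3%.

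**4. The two accounts of reference 25**
- Sample Size: a source for 25% and 30%, which compound to 47.5%.
- Limitations: attrition higher than a level of more than 50%, with no figure given.
- Both cannot describe the same study and the same measure of loss without an explanation.

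**5. Power under heavier loss**

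The article gives no figure above 50%, so the loss rates below are assumptions. Power is for a simple two-group t-test (noncentral t, d = 0.45, alpha 0.05) on the participants remaining in each arm. This is not the repeated-measures F procedure that the section names.

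| Assumed loss | Per arm | Two-sided | One-sided |
|---|---|---|---|
| 50% | 74.0 | 0.776 | 0.860 |
| 55% | 66.6 | 0.732 | 0.826 |
| 60% | 59.2 | 0.680 | 0.785 |

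At the printed 52.5% (70.3 per arm) the values are 0.755 two-sided and 0.844 one-sided.

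Both columns are shown because the article states a 1-tailed test, while its 234 matches a two-sided one. With the normal approximation n = 2[(z₁ + z₂)/d]², where z₁ is the critical value and z₂ = 0.842 is for power 0.80:
- two-sided: 2 × [(1.960 + 0.842)/0.45]² = 77.5, so 78 per arm and 234 in total;
- one-sided: 2 × [(1.645 + 0.842)/0.45]² = 61.1, so 62 per arm and 186 in total.

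**The case against.** The strongest reply is that only a label is wrong. The authors inflated by retention, which is correct, and 444 falls short of 234 by 0.9 of a participant. Two-sided power is 0.796 at 77.7 per arm against 0.797 at 78. This stands. A reader might infer that 444 fails to deliver the 234, but for the losses that the section assumes, the shortfall is rounding.

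Second, a reader might infer that power drops below .80 at the printed 52.5% loss. Under the 1-tailed test as stated, the simple t-test still has 0.84 there, and 62 per arm would suffice, so 444 could lose 1 − 62/148 = 58.1%. Power falls short at that loss only if the 234 is taken as two-sided. This also stands, and the mismatch in sidedness is a separate question. It does not rescue the sentence, because at 52.5% loss the plan's own requirement of 234 is missed whichever test is used.

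Third, a reader might infer that the Limitations section predicts a loss above 50%. It says only that attrition can reach that level, expects this trial to be comparable with online trials, and notes that notifications in the mobile arm may counteract it. The rates are also credited to two studies jointly, and no figure is given for reference 25, so the size of the conflict is unknown. The conflict in wording remains.

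Last, the Statistical Analyses section plans an intention-to-treat analysis with provision for missing data, and a 25% loss at posttest alone leaves 444 × 0.75 = 333, or 111 per arm. The counts of remaining participants may therefore understate the information available. They are nevertheless the basis on which the plan sized the trial.

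**Conclusion.** Wrong as written, in two respects. First, 52.5% is retention presented as attrition, and the equation that leads to it is false. The true allowance is 47.5%, five percentage points less than claimed. At the claimed loss, 23 of the required 234 would be missing (234 − 211). Second, the 25% and 30% attributed partly to reference 25 do not agree with what the Limitations section says about that study.

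The enrolment target is not in error for sequential losses of 25% and 30%. This rests on reading the 30% as a further loss among those still present at posttest, which is the reading that reproduces 444. If 30% were the cumulative loss from baseline, 234/0.70 = 334.3, so 335 would be enough and 444 would leave about 311. Whether power suffers under heavier loss depends on loss rates that the article does not give and on the sidedness of the test.

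**What to change.** 1. Replace the parenthesis in the Sample Size section with wording such as: *sequential retention 0.75 × 0.70 = 52.5%, that is, 47.5% attrition; 444 randomised gives about 233 evaluable (78 per arm)*. Calling the losses sequential also settles how the 30% is meant.
2. Reconcile the 25% and 30% with the Limitations section: say which figure each of the two cited studies supports, and on what definition of attrition.
3. If power under heavier loss is reported, label the loss rates as assumptions and state whether the test is one-sided or two-sided.

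The cost is two or three sentences. Enrolment, design and analysis stay as they are. The authors give up only the claim that a loss of more than half leaves the required number.
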